### Study Conditions and Interventions

#### Overview

The 4 study conditions are displayed in Table 1.

**Table 1 table1:** Study conditions and sample size for the 2×2 factorial trial (n=300).

Study condition	Digital PrEP^a^ locator and digital library	One-on-one individualized peer health navigation	Peer-delivered group-based behavioral intervention	Sample size, n
A: SOC^b^	Yes	No	No	75
B: SOC + PrEP4T^c^	Yes	Yes	No	75
C: SOC + LS4TM^d^	Yes	No	Yes	75
D: SOC + PrEP4T + LS4TM	Yes	Yes	Yes	75

^a^PrEP: preexposure prophylaxis.

^b^SOC: standard of care.

^c^PrEP4T: PrEP for transgender men and transmasculine people.

^d^LS4TM: LifeSkills for Transgender Men and Transmasculine People.

#### Condition A (SOC)

Participants received access to a digital PrEP locator and resource library. The SOC included linkage to the Centers for Disease Control and Prevention’s (CDC’s) HIV Prevention Services Locator, a national directory of HIV testing and PrEP services [8,15,77,78]. A digital library of HIV prevention, sexual health, and antistigma materials (in written and video formats) was also provided. Content was curated from multiple sources, including the CDC [79], Gate Trans Men & HIV Project, UCSF Center for Excellence in Trans Health, and the National LGBTQIA+ Health Education Center. Resources covered transgender community support (eg, support groups), sexual health (eg, contraception, DoxyPEP), HIV prevention (eg, PrEP financial assistance programs, directories of transgender-affirming PrEP providers), and other medical services (eg, gender-affirming care providers). Participants accessed the SOC resource guide on the TOGETHR website through a personal account log-in assigned after randomization. Study staff regularly updated the resources, which could be filtered by topic and location.

#### Condition B (SOC + PrEP4T)

This is an online 1-on-1 peer navigation. PrEP4T was an individualized, TMSM-specific intervention adapted from The Fenway Model [41], consisting of online 1-on-1 sessions between a peer navigator and a participant using a strengths-based case management manualized curriculum (Tables 2 and 3) [80,81]. Peer navigators, employed by Fenway Health and sharing transmasculine community membership with participants, were trained to provide linkages and support. Using an individualized approach, they worked to identify and address barriers, apply an asset-based frame to promote resiliencies, and pragmatically leverage these to improve biomedical HIV prevention outcomes. PrEP4T included 9 hours of content delivered across six 1.5-hour weekly sessions, with peer navigators drawing on techniques from established behavior change models (eg, Motivational Interviewing [82,83]; Transtheoretical Model [84-86]) to support PrEP-related decision-making.

#### Condition C (SOC + LS4TM)

This is an online peer-delivered small group–based behavioral intervention. LS4TM was a theory-based, manualized intervention designed to reduce HIV risk and address mental health–related effects of stigma for TMSM [20]. The program consisted of 9 hours of content delivered through six 2-hour small group sessions (up to 12 participants per group) held weekly for 6 weeks (Tables 2 and 3). While the total content duration was the same as PrEP4T, additional time was allotted for extended group discussions. Sessions were facilitated by staff and contractors employed by Fenway Health, all of whom shared transmasculine community membership with participants.

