#### Condition D (SOC + PrEP4T + LS4TM)

This is an online peer-delivered combined intervention. Participants in this arm received both PrEP4*t* (1-on-1) and LS4TM (group-based) interventions in addition to SOC. Group D received a total of 21 hours of content, consisting of six 2-hour LS4TM sessions and six 1.5-hour PrEP4T sessions. These interventions were not delivered simultaneously within the same 6-week period.

**Table 2 table2:** PrEP4T^a^ intervention sessions: session number, title, content, and conceptual framework guiding the intervention sessions.

Session number	Session title	Session content	Conceptual framework
1	Introduction, Background, and Goal Setting	Build rapport with the participant Assess the participant’s background and sexual health history. Set a realistic, sexual health–related goal for the program (eg, to start PrEP^b^, to consistently communicate with partners about sexually transmitted infection testing). Discuss factors that may impact risk for HIV among transgender men and transmasculine people.	IMB^c^ and Gender Affirmation
2	HIV Transmission and Prevention	Assess what participants know about HIV prevention and how they currently put that information into practice. Introduce participants to the concept of harm reduction. Fill in knowledge gaps and answer questions about HIV prevention. Build on or reinforce participants’ existing harm reduction strategies.	IMB and Healthcare Accessibility
3	Accessing PrEP and Preventive Health Care	Discuss barriers to accessing PrEP and work with participants to identify solutions and options available to them. Provide a brief overview of where and how participants can access postexposure prophylaxis. Discuss preventive health care access, with an emphasis on primary care and sexually transmitted infection testing. Address other preventive care topics, including vaccinations (human papillomavirus, hepatitis A and B), contraception, cervical and anal Papanicolaou testing, and gender-affirming care.	IMB and Gender Affirmation Healthcare Accessibility

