### Statistical Analysis

#### Power

Factorial trials can be powered to detect either main effects or interaction effects, depending on the anticipated influence of interactions within the trial context [92]. This trial was powered to detect the main effects of the PrEP4T and LS4TM interventions. The trial was not powered to detect a PrEP4T × LS4TM interaction effect because (1) based on our conceptualization, the interventions were distinct in delivery (individualized vs group based) and content (peer navigation vs. community support and IMB strategies), and informed by preliminary studies and knowledge of the study population, we did not anticipate a combined interaction effect; and (2) any potential interaction was expected to be negligible, described in factorial trials as a minor “small quantitative interaction” [92-94]. Both PrEP4T and LS4TM were distinct, peer-delivered digital interventions that TMSM endorsed for HIV prevention in our prior research. We hypothesized that each strategy would independently increase PrEP uptake by at least 20% among TMSM, addressing the main-effects research question. Although we did not anticipate interaction effects, we hypothesized additive effects such that participants assigned to the PrEP4T + LS4TM condition would achieve the highest PrEP uptake rates. These superiority hypotheses were supported by evidence from a systematic review of peer-delivered interventions [47].

We estimated PrEP uptake rates in the SOC condition based on prior TMSM data [8,15] and conducted simulations using an SAS macro [95]. Simulations varied the number of participants per condition (n=40-120) and the magnitude of intervention effects over 18 months (20%-40%) for the PrEP4T and LS4TM conditions. Assuming 10% attrition, a total sample size of 300 (75 per condition) provided 80% power or greater to detect a 20% increase in PrEP uptake for each intervention versus SOC at a .05 significance level. We selected a 20% increase because smaller differences were not considered clinically meaningful for potential scale-up. To account for attrition, we planned to enroll 375 participants at baseline, anticipating approximately 20% loss to follow-up, resulting in 300 participants completing the study.

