#### Data Analysis by Aim

We describe the planned analyses by aim.

Before analyses, data will be audited for quality and completeness. Descriptive statistics will be calculated, and variable distributions will be evaluated to ensure they meet the assumptions of planned analytic models, including detection of outliers. In this study, *t* tests and chi-square analyses will be used to assess group equivalence at baseline. Variables showing differences across the 4 groups will be considered for inclusion as covariates in the analyses. All analyses will be conducted using SAS (SAS Institute) or R (R Foundation) software, with statistical significance set at an α level of .05.

Aim 1 analyses will follow an intention-to-treat approach. Random-effects logistic regression will be used with PrEP uptake as the primary outcome. The model will include time (baseline, 6, 12, and 18 months), a categorical variable for study condition (PrEP4T, LS4TM, PrEP4T + LS4TM, with SOC as the reference), and the time × study condition interaction to test whether changes in PrEP uptake over time differ across the 3 intervention conditions compared with SOC. Baseline characteristics that differ across study conditions, as well as variables related to missingness, will be included as covariates if necessary. The primary parameter of interest is the time × study condition interaction term; a significant interaction would indicate that the rate of PrEP uptake over time differs between the intervention and SOC groups. Significant interactions will be graphed and interpreted. We hypothesize that PrEP uptake will be highest among participants randomized to condition D (PrEP4T + LS4TM). The same analytic approach will be applied to the secondary outcome of PrEP adherence. PrEP persistence will be assessed at months 12 and 18 using random-effects logistic regression, including time (12 and 18 months), study condition, and the time × study condition interaction. HIV and sexually transmitted infection incidence will be evaluated using logistic regression, with incidence between baseline and 18 months as the outcome and study condition as the predictor.

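### LS4TM is delivered in groups, but neither the listed Aim 1 model terms nor the power inputs contain a group effect, so LS4TM contrasts are over-precise if outcomes correlate within groups

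*Protocol article*

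**What the plan says.** **Delivery.** The section on Condition C describes LS4TM as "six 2-hour small group sessions (up to 12 participants per group) held weekly for 6 weeks", with extra time set aside for group discussion. The section on Condition D says "Participants in this arm received both PrEP4*t* (1-on-1) and LS4TM (group-based) interventions in addition to SOC". Table 1 puts 75 people in each condition, so 150 of 300 receive LS4TM in groups. Randomization is of individuals, 1:1:1:1. Groups therefore exist on one side of the LS4TM factor only.

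**Analysis.** Data Analysis by Aim specifies a random-effects logistic regression: "The model will include time (baseline, 6, 12, and 18 months), a categorical variable for study condition", plus the time × condition interaction and, where needed, covariates that differ at baseline or relate to missingness. The time × condition term is named as the parameter of primary interest. The level of the random effect is not named. Aim 2 follows the same approach.

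**Power.** The Power section states: "Assuming 10% attrition, a total sample size of 300 (75 per condition) provided 80% power or greater to detect a 20% increase in PrEP uptake". The comparison behind this figure sets either intervention against SOC, tested at the 5% level. The section also says that the trial was powered for the two main effects. The simulations are described as varying the number per condition (40 to 120) and the effect size (20% to 40%). No ICC, group size or design effect appears.

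**The concern.** People who spend six weekly sessions in the same small group share facilitators, peers and discussion. The article's own theory expects this to matter: community connectedness is a proposed mediator, and session notes are to record group dynamics. If the group mechanism works, members' later PrEP uptake should be positively correlated, and 12 people in one group carry less information than 12 independent people.

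With repeated measures per person, the unnamed random effect is most naturally read as a participant effect. That handles correlation within a person, not between members of a group. Followed as written, the plan would then treat group members as independent. Contrasts that involve LS4TM (the LS4TM main effect, C vs A and D vs A) would have standard errors that are too small, tests that reject too often and a stated power that is too high. The trial exists to compare individual with group formats, so the precision attached to the group format matters.

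**Working it through.** **Inputs from the article:** 75 per condition, so 150 per level of the LS4TM factor; groups of up to 12; α = .05; a 20% increase in uptake. **Assumed, because not stated:** two-sided test; 20% means absolute points; ICC of 0.01, 0.02, 0.05 or 0.10; the SOC uptake rates shown below.

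**1. The plan's own figure.** The SOC rate is not printed, so the 80% cannot be reproduced exactly, only tested for plausibility. Without clustering, 75 vs 75 and +20 points gives 87.2% power at an SOC rate of 10%, 81.4% at 15%, 76.7% at 20% and 70.9% at 30%. So 80% against SOC is attainable if SOC uptake is about 16% or lower. At 150 vs 150, power is at least 93.8% for lower-arm rates from 5% to 40%. A relative 20% increase gives under 30% power throughout, so absolute points are the workable reading. Reaching the stated figure does not require a design effect.

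**2. Number of groups.** 150/12 = 12.5, so at least 13 groups if C and D share them; 75/12 = 6.25, so at least 7 per arm if they do not.

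**3. Variance and test error.** The design effect on the LS4TM side is D = 1 + (m − 1) × ICC. With equal arms and only one side grouped, the true SE divided by the naive SE is r = √((1 + D)/2). The true error of a nominal 5% test is 2 × (1 − Φ(1.96/r)). Example: m = 12 and ICC = 0.10 give D = 1 + 11 × 0.10 = 2.10, r = √1.55 = 1.245, 1.96/1.245 = 1.574, and a true error of 11.5%.

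**4. Power of a test that uses the correct SE.** Power = Φ((δ − 1.96 × SE0)/SE1), where SE0 = √(p̄(1 − p̄)(1 + D)/n) and SE1 = √((p1(1 − p1) + D × p2(1 − p2))/n). Example, 20% vs 40% with n = 75:
- D = 1: SE0 = 0.0748, SE1 = 0.0730, z = 0.730, power 76.7%.
- D = 2.10: SE0 = 0.0932, SE1 = 0.0941, z = 0.185, power 57.3%.

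Results for groups of 12:

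| ICC | D | r | True error | C vs A, 10% vs 30%, n = 75 | C vs A, 20% vs 40%, n = 75 | Main effect, 20% vs 40%, n = 150 | Main effect, 30% vs 50%, n = 150 |
|---|---|---|---|---|---|---|---|
| 0 | 1.00 | 1.000 | 5.0% | 87.2% | 76.7% | 96.9% | 94.6% |
| 0.01 | 1.11 | 1.027 | 5.6% | 85.2% | 74.4% | 96.0% | 93.5% |
| 0.02 | 1.22 | 1.054 | 6.3% | 83.1% | 72.1% | 95.1% | 92.2% |
| 0.05 | 1.55 | 1.129 | 8.3% | 77.2% | 65.8% | 91.8% | 88.2% |
| 0.10 | 2.10 | 1.245 | 11.5% | 68.5% | 57.3% | 85.7% | 81.2% |

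The last column is the margin implied by an SOC rate of 20% with both interventions adding 20 points: (20 + 40)/2 = 30% vs (40 + 60)/2 = 50%. Smaller groups soften the effect: m = 8 and ICC = 0.05 give D = 1.35, r = 1.084 and a true error of 7.1%.

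**5. Which group term would correct the primary parameter.** Groups form after baseline, so their influence appears only in follow-up outcomes. Take a linear analogue with two time points, 150 people per side, groups of 10 and an illustrative residual variance of 0.36. A person's change has variance 2 × 0.36 = 0.72, and any group intercept that is constant over time cancels from it. The SE of time × condition is then √((0.72 + 0.72)/150) = 0.098 with or without that intercept. With an illustrative group-by-time variance of 0.10, it becomes √((0.72 + 0.72 + 10 × 0.10)/150) = 0.128. Only the second term moves the SE of the parameter that the plan tests.

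**The case against.** **The article does not exclude a group effect.** It says random effects without naming their level, and a condensed article may leave that structure to a fuller plan. This stands in part: a reader might infer that the plan declares a participant-only random effect, and it does not. But the article lists the model terms, the primary parameter, the simulation inputs and the resulting power, and grouping appears in none of them.

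**No ICC is given and 12 is a maximum.** Participants are individually randomized, recruited nationwide and measured months after a six-week programme, so the correlation could be small; at 0.01 the true error is only 5.6%. This stands as a limit on size. A related argument is that if LS4TM affects nobody, sharing sessions creates no correlation, so the error rates need groups that shift outcomes while averaging to zero. That is correct for a strict null, but the same SE ratio governs interval coverage when there is an effect: a nominal 95% interval would cover about 94.4% to 88.5% over the assumed range.

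**Power was set for main effects.** A reader might infer that grouping leaves the trial underpowered, for instance by discounting from exactly 80%. The documents do not support this. They state 80% or more, and the 150 vs 150 margin starts well above it. C vs A can fall below 80%, but without any grouping it already does so once SOC uptake exceeds about 16%.

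**Funding ended with 103 enrolled.** Restating power for 300 then has limited value for this trial. The analyses are still written in the future tense, however. If the 103 were spread evenly, about 51 would be in C and D, or as few as 5 full groups, which makes the small-sample correction more important.

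**Conclusion.** The point holds as an omission from a stated model and a stated power calculation. LS4TM grouping is fixed by the design and absent from both. Given a positive within-group ICC, LS4TM contrasts are anti-conservative: the naive SE is too small by a factor of about 1.03 to 1.25, and a nominal 5% test errs about 5.6% to 11.5% of the time (assumed ICC 0.01 to 0.10, groups of 12, equal arms, one time point rather than the full longitudinal model).

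The effect on power depends on the contrast. C vs A at 20% vs 40% loses about 2 to 19 points. The LS4TM main effect stays above 80% in both scenarios tabulated, and drops slightly below only in harsher corners at ICC 0.10 (79.9% for 40% vs 60% at 150 per side; 77.0% for 30% vs 50% at 135 per side).

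Two stronger readings are not supported. The article does not show that LS4TM intervals are certainly too narrow, because the ICC is unknown. Nor does it follow that the PrEP4T estimate is sound and the LS4TM one is not: B vs A is untouched by LS4TM grouping, but PrEP4T participants may share navigators, and the hypotheses compare conditions with SOC rather than PrEP4T with LS4TM.

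**What to change.** 1. Record an LS4TM group identifier for everyone in C and D, and state whether the two arms share groups. Session payments and session notes should make membership recoverable.
2. Analyse Aim 1, and the Aim 2 models built on it, as a partially nested design. Name the level of each random effect, and add an LS4TM group effect that acts on post-baseline outcomes in C and D only (a group-by-time effect). An intercept constant over time is not enough, because it would not correct the time × condition term. A group-level cluster-robust variance is an alternative. Either needs a small-sample correction, given few groups.
3. Restate LS4TM power over a range of ICCs and expected group sizes, separately for the main effect and for each comparison with SOC, and print the assumed SOC rate and whether the 20% is absolute.
4. Optionally, add a navigator effect for PrEP4T as a sensitivity analysis.

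The cost is one identifier and one variance component or robust variance. The price is somewhat wider LS4TM intervals and a less favourable stated power. Nothing changes for participants.

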#### Condition D (SOC + PrEP4T + LS4TM)

This is an online peer-delivered combined intervention. Participants in this arm received both PrEP4*t* (1-on-1) and LS4TM (group-based) interventions in addition to SOC. Group D received a total of 21 hours of content, consisting of six 2-hour LS4TM sessions and six 1.5-hour PrEP4T sessions. These interventions were not delivered simultaneously within the same 6-week period.

**Table 2 table2:** PrEP4T^a^ intervention sessions: session number, title, content, and conceptual framework guiding the intervention sessions.

Session number	Session title	Session content	Conceptual framework
1	Introduction, Background, and Goal Setting	Build rapport with the participant Assess the participant’s background and sexual health history. Set a realistic, sexual health–related goal for the program (eg, to start PrEP^b^, to consistently communicate with partners about sexually transmitted infection testing). Discuss factors that may impact risk for HIV among transgender men and transmasculine people.	IMB^c^ and Gender Affirmation
2	HIV Transmission and Prevention	Assess what participants know about HIV prevention and how they currently put that information into practice. Introduce participants to the concept of harm reduction. Fill in knowledge gaps and answer questions about HIV prevention. Build on or reinforce participants’ existing harm reduction strategies.	IMB and Healthcare Accessibility
3	Accessing PrEP and Preventive Health Care	Discuss barriers to accessing PrEP and work with participants to identify solutions and options available to them. Provide a brief overview of where and how participants can access postexposure prophylaxis. Discuss preventive health care access, with an emphasis on primary care and sexually transmitted infection testing. Address other preventive care topics, including vaccinations (human papillomavirus, hepatitis A and B), contraception, cervical and anal Papanicolaou testing, and gender-affirming care.	IMB and Gender Affirmation Healthcare Accessibility
4	Partners and Communication	Define the key components of sexual health to help participants understand how supporting their physical, emotional, mental, and social well-being is part of sexual health. Discuss healthy relationships, partner communication, and boundary setting; share communication strategies and practice communication skills with scripting or role playing. Discuss self-care practices as a tool for managing stressors participants may encounter while communicating their sexual health needs to clinicians and partners, or while navigating the world as a “transgender man or transmasculine person” generally.	IMB and Gender Affirmation
5	Social Support	Identify resources and support systems that can support HIV prevention and sexual health goals. Use self-care practices and positive experiences of our transgender identities to build resilience.	IMB, Gender Affirmation, and Healthcare Accessibility
6	Program Summary and Wrap Up	Summarize program framing and discuss how social stress and IMB concepts connect with the ongoing HIV prevention work the participant has been engaged in. Identify long-term goals, as well as supports and resources participants can access after the conclusion of the program. Solicit verbal feedback, in addition to completion of the session and program feedback forms.	IMB

^a^PrEP4T: PrEP for transgender men and transmasculine people.

^b^PrEP: preexposure prophylaxis.

^c^IMB: Information, Motivation, and Behavioral Skills.

**Table 3 table3:** LS4TM^a^ (small group–based intervention) intervention sessions: session number, title, content, and conceptual framework guiding the intervention sessions.

Session number	Session title	Session content	Conceptual framework
1	Identity Recognition and Affirmation	Provide an overview of the program. Discuss identities and reflect on the diversity of ways participants occupy different identities. Identify the misconceptions and stigmas that exist around the transgender men and transmasculine community, and how these have affected how people feel about their own identities. Discuss factors that may impact risk for HIV among transgender men and transmasculine people.	Gender Affirmation
2	Let’s Talk About Sex	Inform participants about the basics of HIV transmission, barriers, and safer injection practices.	IMB^b^
3	PrEP^c^ for Pleasure	Inform participants about PrEP, postexposure prophylaxis, and contraception. Encourage participants to consider whether PrEP may be right for them. Identify barriers to PrEP use and uptake, and ways to navigate these.	IMB and Healthcare Accessibility
4	Barriers and Opportunities	Learn about setting attainable goals and set a personal goal. Identify roadblocks and structural barriers that impact individual and collective goals and constrain decision-making. Discuss support and resources that can help to overcome roadblocks and barriers to achieving goals.	IMB and Healthcare Accessibility
5	Communication and Partner Negotiation	Identify our rights and responsibilities in relationships. Discuss a variety of partner communication topics relevant to transgender men and transmasculine people, including meeting partners, disclosing identities, educating partners about our transgender identities, and establishing consent and boundaries. Brainstorm and practice healthy partner communication and negotiation skills.	IMB and Gender Affirmation
6	Tying It All TOGETHR^d^	Highlight general sexual health concerns for transgender men and transmasculine people, including healthy sexuality and sexual pleasure. Review the program, then revisit and revise goals moving forward. Gather feedback from participants on the program, the curriculum, and how it was delivered.	IMB

^a^LS4TM: LifeSkills for Transgender Men and Transmasculine People.

^b^IMB: Information, Motivation, and Behavioral Skills.

^c^PrEP: preexposure prophylaxis.

^d^TOGETHR: Transmasculine One-on-One and Group Empowerment for Targeted HIV Reduction.

